## Abstract

**Objectives:**

Many clinical studies have indicated that obstructive sleep apnoea (OSA), the most common chronic sleep disorder, may affect neurocognitive function, and that treatment for continuous positive airway pressure (CPAP) has some neurocognitive protective effects against the adverse effects of OSA. However, the effects of CPAP treatment on neurocognitive architecture and function remain unclear. Therefore, this multicentre trial was designed to investigate whether and when neurocognitive architecture and function in patients with OSA can be improved by CPAP treatment and to explore the role of gut microbiota in improving neurocognitive function during treatment.

**Methods/design:**

This study will be a multicentre, randomised, controlled trial with allocation concealment and assessor blinding. A total of 148 eligible patients with moderate to severe OSA will be enrolled from five sleep centres and randomised to receive CPAP with best supportive care (BSC) intervention or BSC intervention alone. Cognitive function, structure and function of brain regions, gut microbiota, metabolites, biochemical variables, electrocardiography, echocardiography, pulmonary function and arterial stiffness will be assessed at baseline before randomisation and at 3, 6 and 12 months.

**Ethics and dissemination:**

This study has been approved by the Medical Ethics Committee of Shanghai Jiao Tong University Affiliated Sixth People’s Hospital (approval number 2015-79). The results from this study will be published in peer-reviewed journals and at relevant conferences.

**Trial registration number:**

NCT02886156; pre-results.

Strengths and limitations of this studyMulticentre, randomised, prospective study.Relatively large number of participants (n=148).Strictly standardised study population.The multicentre pragmatic design strengthens future results and generalisability.Possible selection bias may exist, as not all possible patients may enter in the study.

## Background

Obstructive sleep apnoea (OSA) is a common chronic sleep disorder characterised by recurrent partial or complete pharyngeal obstruction during sleep.^1^ There is a high prevalence (2%–4%) of this condition in adults aged 30–60 years, which is increasing with the growing epidemic of obesity.^2–4^ OSA is well recognised as a risk factor for neurocognitive, cardiovascular and metabolic disorders.^5–7^ It is worth noting that neurocognitive dysfunction is associated with a series of sequelae, such as social and economic burdens.^8–10^ Continuous positive airway pressure (CPAP) is typically recommended as a first-line treatment for OSA, as it can partly or completely reverse OSA-related complications, including cognitive impairments.^11 12^ In addition, CPAP may be effective for reversing structural and functional brain changes.^13 14^

To date, only two randomised controlled trials (RCTs) have simultaneously evaluated the effects of CPAP on cognition and neuroimaging; both studies had relatively small sample sizes and short intervention periods.^15 16^ However, the response to CPAP treatment in the trials was variable. Thus, the relationships among OSA, brain and neurobehavioural function are complex and must be comprehensively evaluated, including how, when and how long CPAP treatment should be applied for effective therapy.

The gut microbiota is an important factor that affects neurological functions^17^ and may be involved in the modulation of central nervous function (eg, the hypothalamus–pituitary–adrenal axis) and associated with neuropsychiatric conditions.^17 18^ The composition of the gut microbiota is altered through intermittent hypoxia or sleep fragmentation in animal models.^19 20^ However, there have been no studies to determine whether changes in human intestinal microbiota are associated with OSA and whether or how the microbiota can be modulated by CPAP. This study will clarify the complex relationships among OSA, gut microbiota and neurological functions.

## Methods/design

### Study aims and hypotheses

The primary aim of this study is to assess the dynamic (3, 6 and 12 months) effects of CPAP on cognitive function, neurocognitive architecture and function. The primary hypothesis of this study is that, compared with the non-CPAP treatment group, patients with OSA who receive CPAP intervention will show improved cognitive function through structural and functional brain modulation immediately after 3 months of CPAP treatment, and that these benefits will persist at the 6-month and 12-month follow-ups. The secondary aims of this study are to investigate whether and which sleep parameters are correlated with improvements of cognitive function, neurocognitive architecture and function; to explore whether the metabolic status assessed by metabolomics can be reversed by CPAP and correlated with improvement of neurocognitive impairment; and to investigate whether CPAP modulates the gut microbiota and contributes to alleviation of neurocognitive impairment. We hypothesise that patients with OSA who undergo CPAP treatment will have metabolic improvement and modulation of gut microbiota, and that these changes will have beneficial effects on neurocognitive impairment.

### Study design

The Shanghai Multicenter Obstructive Sleep Apnea Therapy trial is a multicentre, evaluator-blinded, randomised, parallel-controlled trial performed in five sleep centres (Department of Otolaryngology and Head and Neck Surgery, Shanghai Jiao Tong University Affiliated Sixth People’s Hospital; Department of Otolaryngology-Head and Neck Surgery, Shanghai First People’s Hospital, Shanghai Jiao Tong University; Department of Otolaryngology, Renji Hospital, School of Medicine, Shanghai Jiao Tong University; Department of Otolaryngology, Head and Neck Surgery, Xinhua Hospital, Shanghai Jiao Tong University School of Medicine; Department of Otolaryngology, The Ninth People’s Hospital Affiliated to Shanghai Jiao-Tong University School of Medicine) in the Shanghai district. The design of this protocol strictly followed the Standard Protocol Items: Recommendations for Interventional Trials^21^ and the Consolidated Standards of Reporting Trials statements.^22^ The study will enrol 148 eligible participants with moderate to severe OSA from the five above-mentioned sleep centres and randomise them to receive CPAP with best supportive care (BSC) intervention or BSC intervention alone. Cognitive function, structure and function of brain regions, metabolites, gut microbiota, biochemical variables, electrocardiography, echocardiography, pulmonary function and arterial stiffness will be assessed at baseline before randomisation and at 3, 6 and 12 months. The flow diagram of this RCT is presented in figure 1.

**Figure 1 F1:**
[figure not shown]
The flow diagram of this randomised controlled trial. BSC, best supportive care; CPAP, continuous positive airway pressure; fMRI, functional MRI; PSG, polysomnography.

### Study population

The study population (30–65 years old) will be enrolled from Shanghai and the surrounding area, and all of the participants will be from the Han population. The diagnostic, inclusion and exclusion criteria for this trial will be as described below.

### Diagnostic criteria

According to the American Academic Sleep Medicine (AASM) 2007 criteria,^23^ moderate and severe OSA are defined as an apnoea–hypopnoea index (AHI) ≥15 and 30 events per hour, respectively, and the normal state is defined as AHI <5 events per hour.

### Eligible participants

#### Inclusion criteria

Informed consentAge 30–65 yearsNewly diagnosed OSA (full-night in-laboratory polysomnography (PSG) with an AHI ≥15 events per hour)Ability to tolerate CPAP treatment based on 1 night of use (must use it for at least 4 hours)No participation in any other clinical trial in the past 3 monthsAble to accomplish relevant tests and follow-up

#### Exclusion criteria

Severe systemic diseases (eg, cardiac, hepatic and renal failure)Psychiatric conditions (eg, depression, mania, schizophrenia)Neurological diseases (eg, head trauma, brain tumour, epilepsy, stroke, transient ischaemic attack, coma)Sleep disorders other than OSA (narcolepsy, insomnia, chronic sleep deprivation, rapid eye movement (REM) behaviour disorder and restless legs syndrome, central sleep apnoea (≥50% of AHI composed of central apnoeas) or obesity hypoventilation syndrome)Alcoholism (according to the National Institute on Alcohol Abuse and Alcoholism, alcoholism is defined as alcohol consumption exceeding 14 standard drinks per week or four drinks per day in men or exceeding seven standard drinks per week or three drinks per day in women. A standard drink was defined as one 12-ounce bottle of beer, one 5-ounce glass of wine or 1.5 ounces of distilled spirits),^24^ drug addiction, use of psychotropic drugs, current sedative use or narcoticsPrior therapy for OSA (ie, CPAP, upper airway surgery, oral appliance)Mini Mental State Examination (MMSE) score <24Left handedMRI contraindications (eg, claustrophobic or metal implantation)Gastrointestinal surgery during the last year, except for appendicitis and hernia surgeryPregnancyUse of intestinal flora regulator (eg, antibiotics or probiotics) in the previous 8 weeksMedical treatment for cholecystitis, gallstones, gastrointestinal ulcers, urinary tract infection, acute pyelonephritis or cystitis in the past 3 monthsInfectious diseases, such as tuberculosis, AIDSCommercial drivers or people deemed to be at risk of driving-related accidentsDeemed by the researchers to be unsuitable for this trial

### Withdrawal criteria

Subjects will be permitted or required to withdraw from this study if they have insurmountable claustrophobia or other unbearable conditions associated with CPAP use, major protocol violation or the development of serious systemic diseases that prevents continuation in this study.

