### Randomisation, allocation concealment and blinding

All eligible patients with moderate to severe OSA will be randomly and equally allocated (randomisation ratio 1:1) to the CPAP plus BSC group or BSC only group. The central random allocation sequence will be produced using the statistical software SAS V.9.4 and managed by an independent statistician (from the Department of Epidemiology, School of Public Health, Shanghai Jiao Tong University) who will be blinded to the participants’ recruitment, evaluation and intervention. The research assistant from each sleep centre will request (via email) a participant’s allocation from the statistician. The group allocation will not be blinded by participants or intervention supervisors in this trial; however, the patients’ group assignments can be blinded to result assessors and statisticians (ie, which patients are allocated to the CPAP treatment versus BSC groups will not be disclosed).

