### Follow-up

At 3, 6 and 12 months during the intervention period, all of the participants will undergo the same examinations as at baseline. During the follow-up period, CPAP usage information will be automatically downloaded daily from auto CPAP via the Internet.

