### Sample size calculation

A previous study indicated that the mean and SD of MoCA score are 26.1 (2.0) and 27.4 (2.3) before and after CPAP treatment, respectively.^27^ With a significance level of 0.05 and statistical power of 0.9, the calculated sample size is 59 for each group. Considering a 20% loss to follow-up, a total of 148 participants will be required for randomisation.

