### Statistical methods

The statistical analysis in this trial will be performed using intention-to-treat (ITT). For missing data, a multiple imputation method will be performed. Normality of the data distribution will be examined by the Kolmogorov-Smirnov test. Continuous variables will be expressed as mean±SD or median (first to third quartile) for normal distribution data or non-normal distribution data, respectively. Categorical variables will be expressed as percentages. To assess primary and secondary endpoints in this trial, a mixed-effects linear model under restricted maximum likelihood and a logistic regression model will be used to analyse the effect of CPAP treatment on the continuous or categorical variables, respectively. In each model, the independent variables should include group (CPAP plus BSC group and BSC group), confounding factors (eg, age, BMI and waist:hip ratio, etc), measurement time (eg, baseline and 3-month, 6-month and 12-month follow-ups) or any other inequality factors between groups at baseline assessment. When a significant main effect was observed, a *post hoc* comparison for different time points (eg, baseline and 3-month, 6-month and 12-month follow-ups) or between groups (CPAP plus BSC group and BSC group) will be performed using multiple comparisons. All of the statistical analyses will be performed using SAS V.9.4, with a two-sided p value<0.05 indicating a statistical significance.

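### The withdrawal rule can end MoCA follow-up, not only CPAP, for CPAP intolerance or protocol violation, which fits poorly with the intention-to-treat analysis and may bias it towards CPAP

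*Protocol article*

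**What the plan says.** **Withdrawal criteria.** The rule reads: "Subjects will be permitted or required to withdraw from this study if they have insurmountable claustrophobia or other unbearable conditions associated with CPAP use". The sentence goes on to two further grounds: "major protocol violation or the development of serious systemic diseases that prevents continuation in this study". What the patient leaves is the study. The closing limit, about being unable to continue, reads most naturally as applying to systemic disease alone. The text does not say which ground makes withdrawal optional and which makes it compulsory.

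**Follow-up.** At 3, 6 and 12 months "all of the participants will undergo the same examinations as at baseline".

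**Statistical methods.** The analysis is declared to be intention-to-treat, with a mixed-effects model for continuous endpoints. On gaps in the data the article says: "For missing data, a multiple imputation method will be performed". It names neither an imputation model nor an assumption about why data are missing.

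**Discussion.** Intention-to-treat is listed among the measures meant to reduce bias.

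**Inclusion and Exclusion criteria.** Entry requires one night of CPAP with at least 4 hours of use. Claustrophobia is given as an example of an MRI contraindication that excludes a patient.

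The primary endpoint is MoCA. No section says that a patient withdrawn for intolerance or protocol violation continues to be assessed on it.

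**The concern.** An intention-to-treat comparison needs outcomes from randomised patients whether or not they tolerated or adhered to treatment. The withdrawal rule ties leaving the study to exactly those two things. Neither CPAP intolerance nor a protocol violation stops someone from sitting a MoCA test, so the missing values would be avoidable.

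The reason for missingness may also be informative. Intolerance of CPAP can arise only where CPAP is used, and a patient who leaves for that reason is one in whom the assigned treatment has failed. If such a patient's scores are filled in from CPAP patients who stayed, the analysis credits a benefit that the patient may not have had. The result would be labelled intention-to-treat but would lean towards the effect in patients who tolerate the device.

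A statistical analysis plan that is not shown could specify the imputation better. It could not recover MoCA scores that were never collected.

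**Working it through.** **1. The plan's own figure.** The Sample size calculation states that "the mean and SD of MoCA score are 26.1 (2.0) and 27.4 (2.3) before and after CPAP treatment, respectively".
- Difference: 27.4 − 26.1 = 1.3.
- Pooled SD: √((2.0² + 2.3²)/2) = √4.645 = 2.155.
- Two-sided alpha 0.05, power 0.90: the normal approximation gives 58 per group. The two-sample t-test gives 89.6% power at 58 and 90.1% at 59, so 59 per group is reproduced.
- With 20% loss: 59/0.80 = 73.75, rounded up to 74 per group and 148 in total, as stated.

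These figures are not in dispute.

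**2. Is the harm lost precision?** Take an extreme case in which the whole planned loss (20% of 148, about 30 patients) falls in the CPAP arm, leaving 44 against 74. Power for a difference of 1.3 is then 88.1%, against 90.1% with 59 against 59. Imbalance in losses alone costs little; the issue is bias.

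**3. Size of the possible bias.** All of the following are assumptions for illustration:
- a share *w* of the CPAP arm is withdrawn for intolerance;
- patients on CPAP gain 1.3 points, and patients off CPAP gain 0;
- withdrawn patients have no MoCA between randomisation and withdrawal;
- imputation gives them the mean gain of the remaining CPAP patients.

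Effect in all randomised patients = 1.3 × (1 − *w*). Estimate after imputation = 1.3. Overstatement = 1.3 × *w* points, or 1/(1 − *w*) − 1 relative to the true value.

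| Assumed *w* | Effect, all randomised | Estimated | Overstatement (points) | Relative |
|---|---|---|---|---|
| 3% | 1.26 | 1.3 | 0.04 | 3% |
| 5% | 1.24 (1.235) | 1.3 | 0.07 (0.065) | 5% |
| 10% | 1.17 | 1.3 | 0.13 | 11% |
| 20% | 1.04 | 1.3 | 0.26 | 25% |

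**4. What moves these figures.** A withdrawn patient who keeps part of the gain, or who has a MoCA at 3 or 6 months, reduces the overstatement. So does an imputation model that uses the CPAP usage data, which the Follow-up section says are downloaded daily. For a given *w*, the table therefore lies at the upper end. The article gives no intolerance rate, so no row can be called the expected one. The 20% row uses up the whole all-cause loss allowance of the CPAP arm. The 1.3 is a before-after change and is used here only as a stand-in for a between-arm effect.

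**The case against.** The best defence is that nothing here is formally inconsistent. Intention-to-treat describes how patients are analysed, and multiple imputation lets withdrawn patients be analysed as randomised. A reader might infer that the rule is a per-protocol exclusion, or that it flatly contradicts the analysis section. The text does not support that: such patients can stay in the analysis set, and withdrawal is permitted or required without either word being assigned to a ground, so removal is not automatic.

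A reader might also infer that the missing data will fall mainly in the CPAP arm. Only the CPAP-related ground is specific to that arm. Protocol violation and systemic disease can occur in both, and no rates are given.

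The CPAP-related ground is narrow, and the one-night tolerance test and the exclusion of claustrophobic patients remove some intolerance before randomisation. Patients who use CPAP poorly but stay in the study still contribute real outcomes. Finally, an imputation model is commonly left to the statistical analysis plan, so its absence from an article is not a fault, and one cannot say outright that imputation will fail.

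All of this stands and limits the size and certainty of the point. It does not answer the central one. The rule as written allows or compels patients to leave the study for reasons of tolerance or adherence, no section keeps them in follow-up, and one night of use says little about 12 months.

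**Conclusion.** The point holds as a stated rule that sits badly with the declared analysis, not as a proven bias. Three sections need reconciling: Withdrawal criteria, Follow-up and Statistical methods. Followed as written, the rule can lose primary outcomes for treatment-related reasons. If the imputation then treats these patients like the remaining CPAP patients, the estimate is shifted in favour of CPAP.

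The size depends on unknowns. Under the assumptions set out in the working, it runs from a few hundredths of a MoCA point at 3 to 5% intolerance to about a quarter of a point at 20%. Treating the upper figure as the expected bias, or saying that the trial will estimate only the effect in CPAP-tolerant patients, would go beyond the documents: the rate, the zero gain off CPAP, the absence of earlier MoCA scores and the imputation model are all assumed.

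Severity: should be fixed. Confidence: moderate.

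**What to change.** Reconcile the three sections by distinguishing discontinuation of CPAP from withdrawal from follow-up. State that patients who stop CPAP or violate the protocol remain in the scheduled MoCA assessments at 3, 6 and 12 months, unless they withdraw consent or cannot be assessed, and that they are analysed in the group to which they were randomised. The clinical decision to stop CPAP is not touched.

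Optionally, add a sensitivity analysis in which CPAP-arm patients who still have missing MoCA after stopping CPAP are imputed from the BSC arm.

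The cost is a small amendment and some effort to keep such patients attending visits already scheduled for all participants. Enrolment was under way when the article was submitted, so scores from anyone already withdrawn may not be recoverable. Retained patients who gain nothing also dilute the observed effect. Under the 20% illustration, power for 1.04 points is 83% if all 74 per arm are followed and 74% with 59 per arm. That smaller effect is nevertheless the one an intention-to-treat analysis is meant to estimate.

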### Recruitment and screening

Participants will be recruited from Shanghai and its vicinity through newspapers and instant messaging software (WeChat). Potential participants with self-reported severe snoring and with an interest in participating will be screened by a standard PSG and examined for eligibility (AHI ≥15 times per hour) for multicentre RCT. Eligible participants will be given a detailed information about this trial.

### Randomisation, allocation concealment and blinding

All eligible patients with moderate to severe OSA will be randomly and equally allocated (randomisation ratio 1:1) to the CPAP plus BSC group or BSC only group. The central random allocation sequence will be produced using the statistical software SAS V.9.4 and managed by an independent statistician (from the Department of Epidemiology, School of Public Health, Shanghai Jiao Tong University) who will be blinded to the participants’ recruitment, evaluation and intervention. The research assistant from each sleep centre will request (via email) a participant’s allocation from the statistician. The group allocation will not be blinded by participants or intervention supervisors in this trial; however, the patients’ group assignments can be blinded to result assessors and statisticians (ie, which patients are allocated to the CPAP treatment versus BSC groups will not be disclosed).

### Intervention

#### BSC only group

Participants in the BSC only group will receive advice regarding lifestyle modification, sleep hygiene, naps, exercise, caffeine and diet and avoiding alcohol consumption, but no specific weight loss programme, diet or salt restriction will be suggested.

#### CPAP plus BSC group

Participants in the CPAP plus BSC group will receive CPAP treatment plus the aforementioned BSC intervention. CPAP treatment (LOTUS AUTO; Curative Medical Technology, Beijing, China) will be initiated using standard clinical practice (before CPAP treatment, the standard clinical practice is for the doctors to educate patients on the use of CPAP and provide positive encouragement) at each centre. Online monitoring of CPAP compliance can also be used to improve compliance. Participants in both groups will be asked to continue their usual medical care during the trial.

### Follow-up

At 3, 6 and 12 months during the intervention period, all of the participants will undergo the same examinations as at baseline. During the follow-up period, CPAP usage information will be automatically downloaded daily from auto CPAP via the Internet.

